| Sample size        | 
Similar research has, by our knowing, has only been done at the ICU. Patients at the ICU will have different reasons for sleep disruption and therefore we cannot use these data to calculate a sample size. Based on our previous research, we aim to include 286 patients in each group.
                                                                                                                                                                                                                                                                                                                                                                                                                                                                                                                               |
| Recruitment        | 
Every workday a researcher will identify together with the treating doctor or intern all potential eligible patients. They will be asked to participate in this project. When patients agree to participate and sign the informed consent document, the patient will receive a sleep registration bracelet for two nights. The following two mornings one of the researchers will visit the patient before 12:00 A.M. for a short interview. The questionnaires will contain questions concerning sleep quality and quantity of the prior night and a month before admission. All data will be registered in the protected Castor database. The results of the sleep registration bracelets will be coded with the record number generated by Castor. The bracelets will be re-used after sterilisation in the hospital.
 |
| Intervention       | 
Interventions:
 
Interventions will be developed in close consultation with clinicians and patients after the baseline data has been collected.
 
Interventions could focus on:
 
 
- Better (comfortable) mattresses/pillows/blankets
 
- Earplugs, sleep masks
 
- Door stops, light strips in hall way, dimmable lights
 
                                                                                                                                                                                                                                                                                                                                                                                                                  |

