|                               | 
 
- Posters to increase awareness with medical team
 
- Sleep education patients (information flyer, inform about possibility to bring own pillow from home, etcetera)
 
- Sleep hygiene training nurses and doctors (awareness, “soft” shoes, use little light, if possible place restless patients in single room, during day time: stimulate patients to leave their beds, open curtains and blinds, discourage afternoon naps and caffeine after 15:00 PM, avoid giving I.V. drips overnight if possible or diuretics in the afternoon if not necessary with the aim of reducing nightly toilet visits, take only vitals when necessary)
 
- Adjust hospital rhythm (only measure vital signs in morning if indicated, wash patients after morning rounds)
 
- Exploring the possibility to use venflon cannulas instead of drips to increase freedom in movement.
 
- ward-specific plan of improvement
 
 |
| Study endpoints        | 
Measurements after first to fifth night:
 
 
- Short questionnaire (see Appendix F1, F2) 
 
o Sleep quality (Patient-Reported Outcomes Measurement Information System (PROMIS™) - based questions (11, 16))
 
o Sleep quantity (Consensus Sleep Diary (CSD)) (11, 17)
 
 
 
- Measured sleep quantity (with sleep tracker (e.g. Actigraph or FitBit))
 
 
After 30 days (from medical record):
 
 
- Length of stay (including discharge diagnosis: homewards/palliative policy/rehabilitation etc)
 
- Incidence of delirium
 
- Incidence of unplanned ICU admissions
 
                                                                                                                                                                                                                             |

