| Other study parameters | Age, sex, number of patients in room, use of sleep medication and other sleep promoting interventions, potential sleep disturbing                                                                                                                                                                                                                                                                                                                                                                                                                                                                                                                                                                                                                                                                                                                                                                                                                                                               |

|                                                |                                                                                                                                                                                                                                                                                                                                                                                                                                                                                                                                                                                                                                                                                                                                                                              |

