|------------------------------------------------|------------------------------------------------------------------------------------------------------------------------------------------------------------------------------------------------------------------------------------------------------------------------------------------------------------------------------------------------------------------------------------------------------------------------------------------------------------------------------------------------------------------------------------------------------------------------------------------------------------------------------------------------------------------------------------------------------------------------------------------------------------------------------|
|                                                | factors (i.e. use of diuretics, drips), MEWS scores, Clinical Frailty index, Charlson Comorbidity Index , clinical diagnosis)                                                                                                                                                                                                                                                                                                                                                                                                                                                                                                                                                                                                                                                |
| Statistical analyses                    | 
Analysis will mainly focus on the first night collected data.
 
Descriptive data-analyses will provide mean, median, 95% confidence intervals (CI) and inter-quartile ranges (IQR) for continuous variables and percentages for categorical variables.
 
Mean difference scores in sleep quantity (Actigraphy) and quality (PROMIS total score) will be compared between groups (intervention- and control group). Confounding and effect modification were assessed using multiple linear regression analysis.
 
Normality will be checked by visual inspection of histograms.
 
p-values of <0.05 will be considered statistically significant. Analysis will be performed using Statistical Package for Social Sciences for Windows (SPSS).
 |

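### The main comparison uses an undefined difference score and gives habitual home sleep, which is collected, no stated role; regression on period adjusted for home sleep would serve better than either reading

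*Protocol*

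**What the plan says.** All references are to the Research information table of the protocol.

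- **Statistical analyses** sets the main comparison: "Mean difference scores in sleep quantity (Actigraphy) and quality (PROMIS total score) will be compared between groups (intervention- and control group". The term for the score is not defined. The row puts the emphasis on first-night data. Its next sentence reads: "Confounding and effect modification were assessed using multiple linear regression analysis". No covariates are named.
- **Recruitment** shows that a pre-admission value is collected: "The questionnaires will contain questions concerning sleep quality and quantity of the prior night and a month before admission". On timing: "The following two mornings one of the researchers will visit the patient before 12:00 A.M. for a short interview". The bracelet is handed out only after consent in hospital.
- **Study endpoints** names the instruments. For quantity: "Measured sleep quantity (with sleep tracker (e.g. Actigraph or FitBit", alongside a self-reported sleep diary. For quality: "Sleep quality (Patient-Reported Outcomes Measurement Information System (PROMIS™) - based questions (11, 16".
- **Other study parameters** begins: "Age, sex, number of patients in room, use of sleep medication and other sleep promoting interventions, potential sleep disturbing". It goes on to illness severity, frailty, comorbidity and diagnosis. Habitual sleep is not in it, but the row lists data to be recorded and does not present itself as a list of adjustment variables.
- **Aim** makes sleep quantity primary. **Design** is before-and-after. **Sample size** is 286 per group.

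**The concern.** The two periods contain different patients who were not randomised. How well a patient usually sleeps is an obvious prognostic variable, and it is recorded. The sentence that fixes the main comparison can be read in two ways, and neither makes good use of that variable.

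- **Hospital minus home, within patient.** For sleep quantity no tracker value exists for home, so a recalled duration would be subtracted from an actigraphic one. A constant offset between the instruments would cancel between periods, but the added noise would not.
- **Plain difference between period means.** Any difference in usual sleep between the two groups stays in the main estimate, and the precision that home sleep could offer is not used.

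The two readings are different estimators, with different variance and different bias under imbalance. For the primary outcome, the choice should be settled before data are seen.

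**Working it through.** **The plan's own figure.** The protocol gives no effect size, SD, power or dropout, so 286 per group can be neither reproduced nor refuted. It can only be back-solved. At two-sided 0.05 and 80% power (both assumed), the detectable standardised difference is (1.960 + 0.842) × √(2/286) = 0.234. At 90% power it is 0.271. The power figures below use 0.234 and assume that the intervention does not change reported home sleep.

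**Assumed inputs (not in the protocol).** ρ is the correlation between home and hospital sleep. k = SD(home)/SD(hospital).

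**Variance relative to comparing the hospital night alone.**
- Difference from home: 1 + k² − 2ρk, which at k = 1 is 2(1 − ρ).
- Home sleep as covariate: 1 − ρ², taking home sleep as balanced between periods.
- Effective n per group = 286 / factor.

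At k = 1:

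| ρ | Difference: factor | Acts like | Power | Covariate: factor | Acts like | Power |
|---|---|---|---|---|---|---|
| 0.2 | 1.60 | 179 | 60.1% | 0.96 | 298 | 81.6% |
| 0.3 | 1.40 | 204 | 65.8% | 0.91 | 314 | 83.6% |
| 0.5 | 1.00 | 286 | 80.0% | 0.75 | 381 | 89.9% |
| 0.7 | 0.60 | 477 | 95.1% | 0.51 | 561 | 97.5% |

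**Break-even.** The difference score is less precise than the hospital night alone when 1 + k² − 2ρk > 1, that is, when ρ < k/2. The threshold is 0.4 at k = 0.8, 0.5 at k = 1 and 0.6 at k = 1.2.

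**Covariate against difference score at k = 1.** (1 − ρ²) / [2(1 − ρ)] = (1 + ρ)/2. At ρ = 0.3 this is 0.65, or 35% less variance. The extra parameter costs a factor of about 570/569 = 1.002.

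**Bias under imbalance.** This is a separate matter from precision and depends on the regression slope of hospital sleep on home sleep, not on the 0.5 threshold. As an assumed example, let the intervention-period patients sleep 15 minutes longer at home, with slope 0.3.
- Plain difference: 0.3 × 15 = +4.5 minutes of bias.
- Difference score: 4.5 − 15 = −10.5 minutes. It over-corrects, as it does whenever the slope is below 1.
- Covariate adjustment removes this component as far as recalled home sleep captures it.

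**The case against.** A reader might infer that the trial ignores home sleep altogether. The protocol does not say so. The difference score may be taken from home, which would use it, and the regression for confounding in the next sentence could include it. The Other study parameters row cannot settle this, because it is a list of recorded data. A covariate list is also commonly left to a statistical analysis plan, which is not at hand, so its absence is no fault. All of that stands. What remains is that the protocol itself fixes the main comparison in terms that allow two analyses, and under either one a better method exists with the data already planned.

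Further limits also stand:

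- The mixed-instrument problem concerns quantity only. For quality, both values come from the questionnaire.
- The difference score is not always poor. At ρ = 0.7 and k = 1 its factor of 0.60 beats the plain comparison and is close to 0.51 for adjustment.
- On the plain-means reading, the gain at ρ = 0.3 is only 9% of variance, and less if home sleep differs between periods.
- Adjustment is not cost-free. Home sleep is asked at interviews after a hospital night, so the answer may be coloured by that night. Patient sleep education is among the possible interventions, so the answer may be coloured by the period too. Recall error leaves residual confounding, and some answers will be missing. A hospital-minus-home score has these same weaknesses.
- In non-randomised groups, change-score and covariate analyses rest on different assumptions, so adjustment is not automatically superior on bias.

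**Conclusion.** The point holds as a defect of definition with a better method available. The main comparison is ambiguous, and habitual home sleep has no stated role in it or in the confounding regression. If hospital minus home is meant, the quantity score mixes a tracker with recalled self-report. At equal SDs it loses precision below a correlation of 0.5 (variance factor 1.40 at 0.3), and it over-corrects imbalance whenever the slope is below 1. If a difference in period means is meant, imbalance in usual sleep stays in the main estimate, and a variance reduction to 0.91 (ρ = 0.3) or 0.75 (ρ = 0.5) is forgone.

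The direction of these results is algebraic. Their size rests on assumed ρ and k and, for the covariate factors, on home sleep being balanced between periods. The documents do not support the stronger conclusion that home sleep is left out, nor that the trial's result would be invalid. This is a cheap improvement that should be made.

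**What to change.** Replace the comparison sentence in the Statistical analyses row with text to this effect:

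- **Quantity:** linear regression of first-night actigraphic sleep time on period, adjusted for self-reported habitual home sleep time. Self-report is not subtracted from actigraphy.
- **Quality:** linear regression of the PROMIS score on period, adjusted for the home sleep-quality score where the questionnaire yields one. The questionnaire appendices are not shown, so this needs confirming.
- **Sensitivity:** report the period estimate without the home-sleep covariate as well, because home sleep is recalled after the hospital night.
- **Missing home values:** state one simple rule, such as imputation, so that patients are not dropped from the main analysis.

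Cost: a few lines of text and one extra model, with no new data collection. The statistical cost is one degree of freedom in about 570. The remaining downside is small: the covariate is recalled and may be affected by the night or the period, which the sensitivity estimate makes visible.

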|-------------------|-----------------------------------------------------------------------------------------------------------------------------------------------------------------------------------------------------------------------------------------------------------------------------------------------------------------------------------------------------------------------------------------------------------------------------------------------------------------------------------------------------------------------------------------------------------------------------------------------------------------------------------------------------------------------------------------------------------------------------------------------------------------------------------------------------------------------------------------------------------------------------------------------------------------------------------------------------------------------------------------------------------------------------------------------------------------------------------------------------------------------------------------------------------------------------------------|
|                   | 
many hospital-related factors such as noise of other patients, noise of hospital equipment, pain and toilet visits (11).
 
A few studies on the effectiveness of interventions to improve the quality of sleep have been conducted in the past, mainly on the Intensive Care (IC) Unit. Interventions such as providing patients with earplugs and sleeping masks, dimming the hallway lights, involving patients in what they need to improve their sleep and implementing sleep hygiene education for nurses have been found to improve both sleep quantity and quality in the IC units (12-15). However, no large scale multicentre studies have been performed on the potential effectiveness of these interventions in regular wards. Therefore, the aim of this study is to implement interventions (such as care-clustering, better mattresses/pillows/blankets, the distribution of earplugs and sleep masks, sleep education to patients, nurses and doctors, adjustment of the hospital rhythm (15)) and to measure whether these interventions have a positive effect on the (experienced and absolute) quality and quantity of sleep in regular hospital wards.
 |

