| Aim        | 
Primary outcome measure:
 
 
- The effect of implemented sleep interventions on the quantity of sleep.
 
 
Secondary outcome measures:
 
 
- To explore the potential effects of the interventions on other sleep outcomes, the use of sleep medication, length of stay (including discharge diagnosis: homewards/palliative policy/rehabilitation etc), incidence of delirium and incidence of ICU admissions from the clinical wards.
 
                                                                                                                                                                                                                                                                                                                                                                                                                                                                                                                                                                                                                                           |
| Design     | 
Before and after study.
 
 
- 8 months baseline measurement
 
- 3 months preparation of interventions
 
- 8 months introduction of intervention and measurement
 
                                                                                                                                                                                                                                                                                                                                                                                                                                                                                                                                                                                                                                                                                                                                                                                                                                                                                                                                                      |

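### The before-after comparison uses methods that, in their usual form, treat patients as independent, although patients on one ward at one time share noise, staff and routines; the stated 5% error rate is therefore probably too optimistic, by an amount that the protocol does not allow to be fixed

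*Protocol*

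**What the plan says.** All references are to rows of the Research information table in the protocol.

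- **Design:** "Before and after study", with "8 months baseline measurement", three months of preparation, then eight months of intervention and measurement. The two groups compared are therefore two calendar periods.
- **Inclusion criteria:** three ward types are named, some in the plural, and other wards may be added. The number of wards is not fixed.
- **Sample size:** "Based on our previous research, we aim to include 286 patients in each group". On earlier intensive-care data the row says "therefore we cannot use these data to calculate a sample size". No effect size, standard deviation, power, ICC or design effect is given.
- **Intervention:** the final package is to be developed after baseline. Most of the listed options change the ward: lighting, door stops, posters, staff training, the hospital's daily rhythm and an improvement plan for each ward. Some, such as earplugs and sleep masks, go to individual patients.
- **Rationale:** poor in-patient sleep is attributed to "many hospital-related factors such as noise of other patients, noise of hospital equipment, pain and toilet visits".
- **Statistical analyses:** means are compared between the two groups; "Confounding and effect modification were assessed using multiple linear regression analysis"; and "p-values of <0.05 will be considered statistically significant". No ward term, time term, random effect or robust standard error is mentioned.
- **Other study parameters:** number of patients in the room is listed. Ward and measurement date are not.

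**The concern.** A comparison of means and an ordinary linear regression both take each patient as a separate piece of information. Patients on the same ward at the same time share neighbours, equipment noise, night staff and routines, and two of the causes in the rationale are of this shared kind. Everyone measured in a given ward-month also belongs to the same period. Any correlation within that ward-month therefore adds variance directly to the period contrast, which is the primary comparison.

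If this is ignored, the standard error is too small, the interval too narrow, and a nominal 5% test rejects a true null hypothesis more often than 5% of the time. At stake is whether a finding of longer sleep after the intervention carries the certainty that its p-value suggests.

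**Working it through.** **The plan's own figure.** The 286 per group cannot be reproduced, because no effect size, standard deviation or power is given. Solving backwards under independence (two-sided 0.05; the protocol does not state sidedness), d = (z₀.₉₇₅ + z_power) × √(2/286). This gives 0.234 for 80% power and 0.271 for 90%.

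**Inputs.** From the protocol: 286 per group, 8 months (about 34.8 weeks) per period, and a 0.05 threshold. Assumed: 3 to 6 wards (k), ICC 0.01 to 0.05, and a correlation c between a ward's effects in the two periods.

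**From design effect to error rate.** If the true variance is DE times the naive one, actual error = 2 × [1 − Φ(1.96/√DE)].

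**(a) Correlation only within ward-weeks.** DE = 1 + (m − 1) × ICC, with m = 286/(k × 34.8).

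| Wards | m | ICC | DE | Actual error |
|---|---|---|---|---|
| 3 | 2.74 | 0.02 | 1.035 | 5.4% |
| 3 | 2.74 | 0.05 | 1.087 | 6.0% |
| 6 | 1.37 | 0.02 | 1.007 | 5.1% |
| 6 | 1.37 | 0.05 | 1.018 | 5.2% |

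**(b) Correlation within ward-months.** Same formula, with m = 286/(k × 8).

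| Wards | m | ICC | DE | Actual error | Effective n per group (286/DE) |
|---|---|---|---|---|---|
| 3 | 11.9 | 0.02 | 1.22 | 7.6% | 235 |
| 3 | 11.9 | 0.05 | 1.55 | 11.5% | 185 |
| 6 | 5.96 | 0.02 | 1.10 | 6.2% | 260 |
| 6 | 5.96 | 0.05 | 1.25 | 7.9% | 229 |

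A simulation with 3 wards (48 ward-months, 2000 runs per ICC) gave naive rejection rates of 7.0% and 11.4% for ICC 0.02 and 0.05. Standard errors clustered on ward-month gave 4.9% and 5.8%.

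**(c) Ward effects that drift between periods.** The same wards appear to serve in both periods, so DE = 1 + (m − 1) × ICC − m × ICC × c, with m = 286/3 = 95.3.

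| ICC | c | DE | Actual error | Interval should be wider by (√DE − 1) |
|---|---|---|---|---|
| 0.01 | 0.8 | 1.18 | 7.1% | 9% |
| 0.02 | 0.8 | 1.36 | 9.3% | 17% |
| 0.05 | 0.8 | 1.90 | 15.5% | 38% |
| 0.01 to 0.05 | 1 | 0.99 to 0.95 | 4.9% to 4.4% | none |

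With 6 wards (m = 47.7) and c = 0.8, the error is 6.0% for ICC 0.01 and 10.1% for ICC 0.05. With 3 wards and c = 0.8, power at d = 0.234 falls from 80% to about 73% (ICC 0.01) or 53% (ICC 0.05). Simulation of (c) with c = 0.8 gave 6.7%, 9.1% and 16.5% for ICC 0.01, 0.02 and 0.05. Adding ward as a fixed effect alone left this unrepaired (6.7%, 9.3%, 17.1%).

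**The case against.** The analysis row is one short paragraph. It does not name the test for the comparison of means, does not say that patients are treated as independent, and ties the regression to confounding and effect modification. A statistical analysis plan that is not shown could add ward and time structure. This stands as a caution about wording: independence is what the named methods assume in their usual form, not something the protocol declares. It does not remove the point, because the protocol does name the methods and the threshold, and these do not fit its own design.

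Stable ward differences largely cancel when the same wards serve both periods with a similar patient mix. This also stands, and it is why the range starts at no inflation. Sharing confined to weeks has only a small effect.

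Three wards is towards the unfavourable end of the assumed range, the package is not final, some components reach individuals, and pain and toilet visits are causes within the patient. All of these may reduce the correlation. They argue for a range and a moderate priority, not for leaving the text as it is.

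A reader might infer a much larger error by treating each ward-period as a separate cluster: with 95.3 patients and ICC 0.01, DE = 1.94 and the error is 16%. That silently sets the correlation between a ward's two periods to zero, which the documents do not support. At a between-period correlation of 0.8, the same ICC gives about 7%.

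**Conclusion.** The point holds as a recommendation. As written, the primary comparison ignores correlation among patients on the same ward at the same time, so its p-value and interval will be too optimistic unless ward effects are perfectly stable.

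The size cannot be determined from the protocol. Under the assumptions shown, the actual false-positive rate is:

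- about 5% to 6% for ward-week correlation (ICC 0.02 to 0.05);
- about 6% to 12% for ward-month correlation with 3 to 6 wards (ICC 0.02 to 0.05);
- about 7% to 16% for 3 wards with ward-by-period drift (ICC 0.01 to 0.05, between-period correlation 0.8);
- not inflated if ward effects are fully stable.

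The upper ends rest on ICC 0.05 and few wards; neither figure is in the document.

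A reader might also infer that repeat admissions of one person add to the problem, since the criteria do not exclude them. The protocol gives nothing on their frequency, so no such claim is made here.

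**What to change.** 1. In the Statistical analyses row, base the primary comparison and its p-value on a linear mixed model with period and ward as fixed effects and a random ward-by-month effect. Alternatively, use the same regression with standard errors clustered on ward-month and a small-sample correction. Apply the 0.05 threshold to this model.
2. Add ward and measurement date to Other study parameters. The model cannot be fitted without them, and neither is listed now.
3. State as a limitation that, with few wards and a single switch from before to after, ward-by-period drift cannot be separated from the intervention effect. The proposed model handles correlation within ward-months; it does not remove that drift.

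**Cost:** a few sentences and two recorded variables, with no extra patients or procedures. Intervals will be somewhat wider: in case (b) by a factor √DE, from about 1.05 (6 wards, ICC 0.02) to 1.24 (3 wards, ICC 0.05).
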